## Abstract

**Background:** Older adults, including those with Alzheimer’s disease and Alzheimer’s disease-related dementias (AD/ADRD), face barriers in maintaining regular physical activity, which increases their fall risk and reduces their quality of life. The Activity Tracking, Care Partner Co-Participation, Text Reminders, Instructional Education, Video-Guided Physical Rehabilitation, and Exercise trial aims to improve physical activity among older adults. This pilot study aims to assess the feasibility and preliminary efficacy of the ACTIVE intervention. **Methods:** ACTIVE is a multi-method, two-arm randomized, analyst-blinded crossover pilot trial with an embedded qualitative component. We will recruit 50 community-dwelling dyads (older adult–care partner, n = 100), with and without mild AD/ADRD, in a 1:1 ratio. Each dyad will be randomized to the intervention or control arm, stratified by AD/ADRD diagnosis. The intervention arm will receive activity tracking, motivational texts, walking exercises, educational videos, and video-guided physical rehabilitation sessions, while the control arm will receive only activity tracking. The intervention will run in two halves: a three-week intervention/control, a one-week crossover phase, and a three-week control/intervention phase. The quantitative outcome measures will include feasibility measures (recruitment, adoption, adherence, acceptability, fidelity, and retention), and measures of preliminary efficacy (activity metrics, fall risk and fear of falling, functional limitations, and quality of life). Qualitatively, we will assess participants’ experiences, and facilitators and barriers to engagement in physical activity through semi-structured dyadic interviews and thematic analysis. **Conclusions:** This pilot study will generate data on the feasibility and preliminary efficacy of the ACTIVE trial. Findings will inform a full-scale implementation trial.

## 1. Introduction

Physical activity is a well-established determinant of health and functional independence among older adults [1,2]. However, older adults face significant barriers to maintaining regular physical activity, including symptoms of chronic disease, mobility limitations, and challenges with motivation, activity initiation, and maintenance [3,4,5]. These challenges are particularly pronounced among persons living with Alzheimer’s disease or Alzheimer’s disease-related dementias (AD/ADRD), who are at a 2- to 4-fold higher risk of falls and poorer quality of life compared to those without AD/ADRD [6,7]. Malnutrition, a geriatric syndrome associated with sarcopenia, functional vulnerability, and biological frailty [8], further contributes to reduced functional status and quality of life in older populations [9]. Despite evidence supporting the benefits of physical activity in reducing fall risk [10,11], and enhancing overall quality of life [12,13], adherence remains a challenge, particularly for older adults with AD/ADRD who may require additional support to maintain activity routines.

Improving physical activity among older adults requires approaches grounded in established behavioral theory. The Social Cognitive Theory (SCT) is one such theory, and it describes behavior as the product of continuous interactions among personal, behavioral, and environmental factors [14]. Within the personal domain, constructs such as self-efficacy and outcome expectations shape an individual’s confidence and beliefs about the benefits of being active [15,16]. The behavioral domain includes self-regulation skills, such as goal-setting, self-monitoring, and adjusting one’s actions based on feedback, that support sustained engagement in physical activity [15,16]. The environmental domain encompasses external influences, such as social support, modeling, and reinforcement, that can facilitate adherence to physical activity [15,16].

Using the SCT, we designed a multi-component intervention that comprises Activity tracking, Care partner co-participation, Text reminders, Instructional education, Video-Guided Physical Rehabilitation, and Exercise (ACTIVE). ACTIVE targets the personal domain through instructional education (I) and text reminders (T), the behavioral domain through structured walking exercise (E), and activity tracking (A), and the environmental domain through care partner co-participation (C) and video-guided physical rehabilitation (V) (Figure 1). These components are particularly relevant for older adults with mild AD/ADRD, whose cognitive impairment may not substantially impact their understanding of activity instructions.

Empirical evidence suggests that wearable activity trackers, such as Fitbit smartwatches, improve self-monitoring, with preliminary studies showing higher step counts and greater adherence to physical activity among older adults [17,18,19]. Motivational text messages have been shown to reinforce behavior, provide reminders, and sustain activity among older adults [20,21,22]. Virtual physical therapy offers a scalable approach to improving strength, balance, and mobility by delivering structured, remotely tailored exercise programs [23,24,25]. Walking exercise provides a simple, evidence-based strategy to increase daily physical activity, improve cardiovascular fitness, reduce the severity of fall injuries, and reduce the fear of falling [21,26]. Care partner involvement further enhances adherence, provides social support, and ensures safety, with dyadic interventions demonstrating improved outcomes in physical activity and health management [27,28]. Together, these components of the ACTIVE intervention target both behavioral and functional pathways to reduce fall risk and improve quality of life among older adults.

By integrating wearable technology, video-guided physical rehabilitation, walking exercise, text reminders, education, and care partner co-participation, the ACTIVE intervention has the potential to improve physical activity engagement, reduce fall risk, and improve the quality of life of older adults with and without mild AD/ADRD. The project will contribute to the growing evidence on digital health interventions for aging populations and inform the development of scalable strategies to promote physical activity among older adults (care recipients) and their care partners. To our knowledge, no prior intervention has employed a theory-guided, multi-dimensional approach to simultaneously improve physical activity, reduce fall risk, and improve quality of life for older care recipient–care partner dyads with and without mild AD/ADRD. This pilot study has two aims. First, we aim to examine the feasibility (i.e., recruitment, adoption, adherence, acceptability, fidelity, and retention) of the ACTIVE intervention among older care recipient–care partner dyads with and without mild AD/ADRD. Second, we aim to evaluate the preliminary efficacy of the intervention on perception, attitudes, and engagement in physical activity, fall risk and fear of falling, and quality of life in these dyads.

## 2. Materials and Methods

For this remote, home-based, technology-assisted intervention, we will conduct a multi-methods pilot study using a two-arm, crossover, analyst-blinded randomized controlled trial with embedded qualitative interviews. The study population will consist of community-dwelling older care recipients and their care partners (dyads) with and without mild AD/ADRD. Our study population will be recruited from ResearchMatch, a national, NIH-funded volunteer registry that connects researchers with individuals interested in participating in health-related studies [29]. It has over 120,000 volunteers, including over 13,000 older adults and 700 with self-reported AD/ADRD [29]. We will send recruitment emails weekly and enroll participants on a rolling basis until we reach our target sample size.

### 2.1. Eligibility Criteria

Eligible care recipients will be aged 65 years or older, English or Spanish-speaking, community-dwelling, and have no contraindications to engaging in physical activity. They must be willing to wear a smartwatch, receive text messages, watch intervention-related videos, and participate in video-guided physical rehabilitation sessions and walking exercises. Care recipients will be ineligible if they do not have a care partner or have severe cardiac, neurologic, or musculoskeletal conditions (including, but not limited to, a recent joint replacement or recent or untreated fractures in any part of the body) that limit participation in walking exercise or smartwatch use. Also, they will be excluded if they have moderate to severe dementia and are unable to operate or manage a smartwatch even with care partner support. Additionally, they will be excluded if they have no internet, phone, or any devices capable of receiving text messages or watching educational or physical therapy-related videos.

Similarly, eligible care partners must be at least 18 years old. They must be the legally authorized representative of the care recipient when the care recipient lacks the capacity to consent. They must live with or within five miles of the care recipient and be able to co-participate in all aspects of the ACTIVE intervention. They will be ineligible if they have severe cardiac, neurologic, or musculoskeletal conditions (including but not limited to recent or untreated fractures in any part of the body), limiting participation in walking exercise or smartwatch use. Also, they will be excluded if they have moderate to severe dementia, are unable to operate or manage a Fitbit smartwatch, have no internet, phone, or any device capable of receiving text messages or watching educational or physical therapy-related videos.

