### 2.5. Intervention Design

The ACTIVE intervention consists of six co-occurring events as follows (Table 1):

Activity Tracking: Care recipients and their care partners will be provided with a wrist-worn Fitbit smartwatch to wear during waking hours for at least 8 h per day. Activity metrics will be tracked for care recipients and care partners on Fitabase.

Care partner co-participation: Care partners will play active, structured roles in the intervention. These roles include (1.) Safety oversight, (2.) Co-engagement, (3.) Education access and (4.) Motivation and supervision. Care partners will be required to ensure their care recipients use the smartwatch consistently, walk safely, and adhere to exercise protocols (safety oversight). They will participate in walking exercises and video-guided physical rehabilitation sessions together with their care recipient (co-participation). They will view educational videos to understand how best to support care recipients to stay active in safe environments (education). Lastly, they will encourage adherence, monitor fatigue, and help adjust routines as independence improves (motivation and supervision). Care partner engagement will be assessed using a multimodal approach, including platform-based analytics (login frequency, module completion), structured prompts embedded within myACTIVEsteps, and brief scheduled daily text message check-ins to capture real-time participation and support activities.

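### Section 2.1 requires care recipients, but not care partners, to be free of contraindications to physical activity, although both do the same exercise

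*Protocol article*

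**What the plan says.** Section 2.1 of the protocol article gives a separate eligibility list for each member of the dyad.

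- **Care recipients** have this inclusion rule: "Eligible care recipients will be aged 65 years or older, English or Spanish-speaking, community-dwelling, and have no contraindications to engaging in physical activity". They are also excluded for severe cardiac, neurologic or musculoskeletal conditions, with the examples "a recent joint replacement or recent or untreated fractures in any part of the body) that limit participation in walking exercise or smartwatch use".
- **Care partners** have a paragraph that opens as a parallel to the one before it. It sets an age floor ("eligible care partners must be at least 18 years old") and requires them to "be able to co-participate in all aspects of the ACTIVE intervention". It excludes severe conditions of the same three kinds, again "limiting participation in walking exercise or smartwatch use". It contains no criterion on contraindications to physical activity.

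Section 2.5 makes the exercise a shared task. Of care partners it says: "They will participate in walking exercises and video-guided physical rehabilitation sessions together with their care recipient". Under its virtual physical therapy component, both members are expected at each session. Section 2.3 has all participants switch arms after the first phase.

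**The concern.** The two members are assigned the same walking and the same gait, strength and balance videos, but the test of whether physical activity is contraindicated is applied to only one of them. Section 2.1 gives no reason for the difference.

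What is at stake is the safety of the care partner. There is also a second-order effect on the care recipient, because Section 2.5 gives the care partner safety oversight of the recipient's walking and exercise. The rehabilitation videos are asynchronous (Section 2.4), so no staff member is described as watching the sessions live. No estimand, model or precision statement depends on the point.

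**Working it through.** **Who is exposed.** Section 2.8 plans 50 dyads of two people: 50 × 2 = 100 participants, which agrees with the stated n = 100. Care partners are 50/100 = 50%. Because of the crossover, all 50 are assigned the intervention in one of the two three-week phases. The figure of 50 is the number to whom the contraindication criterion is not applied. It is not the number with a contraindication.

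**What each list does.** Take a person who has some contraindication to physical activity. As a care recipient, that person is barred in every case by the inclusion criterion. As a care partner, there are three cases:

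| Case | Care recipient | Care partner |
|---|---|---|
| (a) Severe cardiac, neurologic or musculoskeletal condition limiting walking or watch use | Barred | Barred by the exclusion |
| (b) Not (a), but unable to do some component | Barred | Barred by the ability requirement |
| (c) Able to do every component, and the condition is not severe, or is outside the three kinds, or does not limit walking or watch use | Barred | No listed criterion applies |

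The lists differ only in case (c).

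**Is (c) an empty case?** The protocol's own structure says not. Care recipients face both the contraindication criterion and the exclusion for severe limiting conditions, so the document treats a contraindication as something other than a severe limitation. For care partners it keeps the second test and replaces the first with one of ability. A person can be able to do an exercise that is inadvisable for them.

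**How large is (c)?** The documents give no care partner age distribution beyond the floor of 18 years, and no rate of contraindications. Any rate applied to all 50 partners would also count those already removed under (a) and (b). No number can be derived, and none is offered.

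**The case against.** The case on the other side is substantial.

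- **The ability requirement.** It covers all aspects of the intervention, and so includes the strength and balance videos. In an exercise trial, being able to take part may be read as being able to do so safely. This stands in part: it closes case (b) and makes the gap narrow. It does not close case (c) on the wording, because Section 2.1 states absence of contraindications as a criterion in its own right for the other member.
- **Different populations.** Care recipients are 65 or older and 25 of the 50 are to have mild dementia, while care partners may be any adult age. A different rule for the two roles could be a deliberate choice. That is why stating the reason would be an adequate answer; at present none is given.
- **Low risk and monitoring.** Section 2.14 describes a minimal-risk intervention with ethics approval and monitoring of harms, and Table 2 has weekly telephone check-ins. This lowers the weight of the point. Monitoring acts after entry, however, and does not replace an entry criterion.
- **A condensed article.** Detailed screening forms may sit in the full protocol. But the article sets out both lists explicitly and they differ, so the point does not rest on omitted detail.

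A reader might also infer more from the two lists than they support. The care partner examples do not name recent joint replacement, but those examples are expressly not exhaustive, so leaving one out does not change the rule. The reference to walking and smartwatch use stands in both exclusions and is not a weakness particular to care partners.

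**Conclusion.** The point holds in a limited form. The contraindication criterion is fixed for one exercising member of the dyad and not for the other, with no reason given. The practical gap is confined to care partners who can do the exercise but have a contraindication that is not a severe, limiting cardiac, neurologic or musculoskeletal condition. Their number is unknown. The conclusion assumes that ability to take part is not meant to include absence of contraindication, which is the plain reading of two separately worded criteria.

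Two stronger readings are not supported:

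- **That care partners enter with no safety rule, or that half of the sample is at risk.** Two criteria in Section 2.1 do protect them, and 50 of 100 only counts those to whom the third is not applied.
- **That a partner who has to stop exercising takes the dyad out of the trial and lowers retention.** Section 2.6 withdraws the dyad when a member chooses to discontinue participation, and Section 2.9 foresees partial discontinuation with key outcomes still collected where possible. A loss of retention does not follow from the text.

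This is a modest safety and consistency point that is cheap to correct and worth correcting before enrollment.

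**What to change.** Reconcile the two paragraphs of Section 2.1 so that the contraindication criterion is addressed for both members who exercise, or state why it differs between them. What counts as a contraindication, and whether the two roles should have the same rule, is a clinical decision for the sponsor and investigators. Then bring the enrollment check in Section 2.2 into line, so that whatever is decided for care partners is asked of them before randomization.

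The cost is about one sentence of eligibility text and one matching enrollment item. If the sponsor extends the criterion to care partners, a few dyads may become ineligible; the documents do not allow that number to be estimated.

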### 2.2. Screening, Recruitment, and Enrollment

Screening, recruitment, and enrollment will be rolling for 12 months or until we obtain 50 dyads—25 older adults and care partners without mild dementia (25) and with mild dementia (25). Screening will start with a recruitment email that includes the eligibility requirements sent to potential participants registered on ResearchMatch. Those interested in the study will provide their email addresses, and a formal email with a screening and recruitment survey link will be sent to them. The screening survey will include a brief questionnaire requesting their age, caregiving status, language preference, willingness to participate in a physical activity intervention and/or survey, and access to a smartphone or computer. Those who meet the eligibility criteria will gain access to the recruitment survey.

The recruitment survey will request their email and phone number, ask for the name, email address, and phone number of their care partner/care recipient, and request a preferred date for the video enrollment session. Text messages and emails will be automatically sent to the listed care recipient and care partner to confirm participation in the enrollment video session. Within 48 h of the care recipient and the care partner completing the survey, the dyad will receive emails and text messages confirming the date and time of the video enrollment session.

This video enrollment session will include a member of the study team and the two members of the dyad. If either member is unavailable, the study team member will reschedule the call. Both members must be visible in the video call to establish a dyadic enrollment. During the video enrollment session, the study team member will explain the study intervention in lay terms and obtain consent for participation. For care recipients with self-reported dementia, the study team member will administer the Ascertain Dementia-8 questionnaire (AD-8; score ≤ 4) [30] or the Clinical Dementia Rating (CDR; score ≤ 1) [31] to verify whether dementia is mild. For those with an AD-8 score of ≤4 or a CDR ≤ 1, the study team member will assess capacity to consent using the University of California San Diego Brief Assessment of Capacity to Consent (UBACC) [32]. A score of 14.5 out of 20 is required to be eligible to consent [32]. Those with a score ≤ 14.5 will require a care partner who is their legally authorized representative to provide consent for participation.

Dyads that consent will complete a self-administered baseline survey (discussed below). Also, during the video call, the study team will guide the care recipient and care partner in creating user accounts on myACTIVEsteps.com and Fitabase, and on the Fitbit smartwatch (discussed below), using their preferred names, user identities (IDs), and phone numbers. Each video enrollment session is expected to last between 45 and 60 min. After the video call, the study materials (Fitbit smartwatch, educational materials on fall prevention, and instructions for accessing the online videos and using the smartwatch) will be sent to study participants within 1 week of enrollment. All surveys and consents will be administered remotely on Research Electronic Data Capture (REDCap) [33]. All study participants will be informed that de-identified ACTIVE study data may be used for future ancillary studies without additional participant contact, subject to IRB approval.

### 2.3. Randomization

Participants will be assigned to study arms after completion of the baseline enrollment survey. The study staff who enrolls each participant will notify the study biostatistician, who will provide the allocation. Randomization will be conducted using a computer-generated, permuted block randomization sequence stratified by dyad type (with or without mild AD/ADRD). Within each stratum, randomization will be performed using permuted blocks of 4 to ensure balanced group sizes. Both members of the dyad will be randomized together to the same intervention or control arm. The randomization sequence will be generated in advance by the study biostatistician using a random number generator and securely maintained within the study database, accessible only after baseline data collection is completed. After the third week of intervention, we will have a one-week crossover period, and all participants will switch to the alternate study arm. This one-week crossover period is a washout period to minimize the effects of promptings and motivations produced by the text messages, rather than to eliminate retained knowledge or behavior change. Group assignments will remain linked to each participant’s unique study ID throughout the study. The analyst will remain blinded to group assignments until data cleaning, feasibility, and preliminary efficacy analyses are complete.

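### A fixed, published block size of 4 lets an enroller who knows all earlier allocations in a stratum deduce up to about 32% of allocations in advance; varying, withheld sizes are a cheap improvement

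*Protocol article*

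**What the plan says.** Section 2.3 of the protocol article describes a computer-generated permuted-block list with two strata, dyads with and without mild AD/ADRD. It gives one block size: "Within each stratum, randomization will be performed using permuted blocks of 4 to ensure balanced group sizes". The unit is the dyad: "Both members of the dyad will be randomized together to the same intervention or control arm". Section 2.2 sets the target at 25 dyads in each stratum, 50 in all.

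On how an allocation is obtained, section 2.3 says: "The study staff who enrolls each participant will notify the study biostatistician, who will provide the allocation". Assignment follows the baseline survey, and the list is "securely maintained within the study database, accessible only after baseline data collection is completed".

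Only the analyst is described as blinded. Under section 2.6, control dyads have the smartwatch alone, without texts, education or rehabilitation videos, so the arm is visible to dyads and to the staff in contact with them.

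In the enrolment video session (section 2.2), a study team member explains the study and obtains consent. Where the care recipient reports having dementia, a check of its severity follows: "the study team member will administer the Ascertain Dementia-8 questionnaire (AD-8; score ≤ 4) [30] or the Clinical Dementia Rating (CDR; score ≤ 1". Capacity to consent is assessed next.

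Section 2.13 takes the effect size from the pre-crossover phase.

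**The concern.** With a single known block size, the remaining places in a block follow from those already filled. Once both places of one arm are used, the rest of the block is fixed. The size is printed in a public article and there are only two sequences to follow. A staff member who has seen the earlier allocations in a stratum can therefore sometimes know the next arm before the next dyad is enrolled. Keeping the list locked stops anyone reading ahead; it does not stop this deduction.

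The same staff role has some influence, although limited, over which dyad takes the next place: how the study is explained, which of two dementia instruments is used, the capacity assessment, and rescheduling when a dyad member is unavailable. If that influence were used in the light of a known arm, the arms could differ at entry in ways the models do not capture, such as motivation. The pre-crossover comparison is a parallel-group comparison of about 25 dyads per arm. The later crossover does not protect it, and section 2.13 intends its estimates to inform power calculations for the definitive trial.

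**Working it through.** The article gives no figure for predictability, so there is none to reproduce.

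**Inputs**
- Block size 4, one fixed size (section 2.3).
- Two places per arm in each block. This is read from "permuted blocks of 4 to ensure balanced group sizes" with two arms; section 2.3 does not write the ratio out.
- Two strata of 25 dyads (sections 2.2 and 2.3), so each stratum is 6 complete blocks plus 1 dyad.
- Upper-limit assumption: one enroller knows every earlier allocation in the stratum.

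**Step 1. One block of 4.** The 6 possible arrangements are equally likely.

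| Place in block | Chance the arm is already certain | Chance a best guess is right |
|---|---|---|
| 1 | 0 | 1/2 |
| 2 | 0 | 2/3 |
| 3 | 1/3 | 2/3 |
| 4 | 1 | 1 |
| Sum | 4/3 | 17/6 |

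Per complete block, (4/3)/4 = 33.3% of allocations are certain, and best guessing is right (17/6)/4 = 70.8% of the time.

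**Step 2. The planned strata.**
- Certain allocations per stratum: 6 × 4/3 + 0 = 8 of 25 (32%). Over both strata: 16 of 50.
- This is an average. Over the 12 complete blocks the number lies between 12 (only the fourth place certain in every block) and 24 (third and fourth certain in every block).
- Best guess per stratum: (6 × 17/6 + 1/2)/25 = 17.5/25 = 70%, against 50% by chance.

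**Step 3. Partial knowledge.** Suppose an enroller knows each earlier allocation with probability f. The arm is certain only if the two same-arm places already used were both seen, which has probability f². The certain share per complete block is then (f²/3 + f²)/4 = f²/3.
- f = 1: 33.3%
- f = 1/2: 8.3%
- f = 1/3: 3.7%

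**Step 4. Varying block sizes.** Lists of 25 were simulated (4,000 runs). The guesser knows which sizes are possible but not their order, and updates exactly after each allocation.

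| Scheme | Certain | Best guess right |
|---|---|---|
| Fixed 4 | 32% | 70% |
| Random 4 and 6 | about 6% | about 68% |
| Random 4, 6 and 8 | about 2% | about 67% |

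A larger fixed size helps less with certainty: a fixed block of 6 still leaves 24% certain at 25 dyads, and a fixed block of 8 leaves 19%.

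**Step 5. Imbalance at 25 dyads.** With blocks of 4, dyad 25 opens a new block after six balanced ones, so the imbalance is exactly 1. With random sizes 4 and 6, an imbalance of 3 needs dyad 25 to be third in a block of 6 (probability 0.203) with the first three places all in one arm (2/20 = 0.1). That gives 0.203 × 0.1 = 0.020, about 2% of lists per stratum.

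**The case against.** The strongest case against giving this much weight has five parts.

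- **Knowledge is assumed.** The 32% needs one person to know every earlier allocation in a stratum. The article does not say how many staff enrol, and step 3 shows how fast the share falls when knowledge is split. This stands, and the figure is stated only as an upper limit.
- **The recipient is inferred.** A reader might take it as stated that the enroller is told the arm. Section 2.3 says who asks and who provides, but not who receives. The enroller is the natural reading, no more.
- **Discretion is limited.** A reader might infer that the enroller controls the order of entry. Section 2.2 does not support that: dyads request their own date, confirmation messages are sent automatically, and staff reschedule only when a member is unavailable. AD-8, CDR and the capacity assessment have stated cut-offs, and the dementia check applies only to self-reported dementia. Some discretion remains, because no rule is given for choosing AD-8 or CDR.
- **Motive and consequence are modest.** Every dyad is scheduled to receive the intervention. The models adjust for baseline outcome, dementia status and covariates that include frailty and comorbidity. The article says the trial is not powered for efficacy, and most feasibility benchmarks are not between-arm contrasts. This lowers the severity. It does not remove the exposure of the pre-crossover estimate, because adjustment reaches only what is measured.
- **The remedy hardly reduces guessing.** Best-guess accuracy moves only from 70% to about 68%. This is correct; the gain is mainly in certainty.

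**Conclusion.** The point holds as a low-severity weakness with a cheap remedy. A fixed, disclosed block size of 4 in two strata makes up to about 32% of allocations (16 of 50 dyads on average) certain before enrolment, and best guessing right 70% of the time. Both figures assume two places per arm in each block, 25 dyads per stratum, and one enroller who knows all earlier allocations in the stratum. With knowledge of a random half, the certain share is about 8%; with a third, about 4%.

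The planned lock on the list does not address this, because the deduction uses past allocations and not the list. The part of the trial exposed is the pre-crossover effect estimate.

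A reader might go further and conclude that a third of allocations will be known, or that the effect estimate will be biased. The documents support neither. They do not show that any enroller holds the full allocation history, and no size of bias can be derived from them.

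**What to change.** In section 2.3, replace the fixed size with randomly varying block sizes within each AD/ADRD stratum, for example 4 and 6. State that the sizes are withheld from enrolling staff until enrolment ends. If enrolment has begun, apply this to the unused part of the list.

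Release of each allocation only after the baseline survey is already planned and needs no change.

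The cost is regenerating the list and amending a sentence. The statistical price is that the imbalance in a stratum of 25, exactly 1 under blocks of 4, would be 3 in about 2% of lists. In return, the share of allocations that can be known with certainty falls from an upper limit of 32% to about 6%.
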